These adaptive models are crucial because evidence suggests that the most effective interventions are those that include multiple components and can tailor the narrative to individual needs [22,23]. In healthcare education, the incorporation of advanced high-fidelity simulators with structured feedback mechanisms and continuous assessment is vital to refining technique and fostering clinical decision-making skills [24]. Recent innovations include using artificial intelligence for adaptive responses in simulation environments, indicating a trend towards personalized and sustainable competency-based training strategies [25]. This paradigm shift aligns directly with the emerging concept of ‘Precision Medical Education’, which emphasizes the use of technology and continuous data streams to tailor educational trajectories to the specific needs of each learner [26,27]. Employing an approach that combines individualized measurement, through the PPDS [21], with adaptability enables the design of personalized gamified experiences that improve learning and interaction in the classroom, optimizing professionals’ ability to acquire the necessary competencies [14] and improve their quality of care in clinical practice.

Current research has reached a saturation point regarding the general efficacy of gamification versus traditional methods, yet a critical gap remains in understanding how to optimize these interventions for diverse types of learners. Generic gamification carries inherent risks: if the game mechanics do not align with the student’s intrinsic motivation, it can lead to frustration, cognitive overload, or disengagement, potentially mitigating the educational benefits.

This study is necessary and timely because the recent maturation of Generative Artificial Intelligence (AI) finally enables scalable and sustainable personalization of clinical narratives—a feat previously considered too resource-intensive for standard curricula. The novel and testable contribution of this protocol is the shift from a binary comparison (game vs. no game) to a nuanced analysis of mechanics–profile fit. Therefore, generic gamification was chosen as the active comparator to isolate and quantify the specific added value of the ‘personalization’ variable.

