### 2.5. Randomization and Masking

Given the nature of practical teaching (in which groups are pre-established by enrollment), simple individual randomization is not possible. Therefore, a cluster randomization design will be implemented. An independent researcher not involved in the teaching process will use (RANDOM.ORG; Randomness and Integrity Services Ltd., Dublin, Ireland) computerized random number generation software to assign the practice shifts (clusters) to either the CG or EG arm. Allocation concealment is ensured as the assignment will only be revealed to the Principal Investigator and students on the first day of the intervention.

Given the highly experiential nature of the intervention, participant blinding to the educational differences between conditions is likely only partial. However, participants will remain naive to the comparative study hypothesis and their specific allocation to either the control or experimental cohort. However, due to the logistical requirements of the intervention (the distribution of specific login codes), the Principal Investigator (PI) cannot be blinded during the sessions. To mitigate bias and ensure external control, statistical data analysis will not be performed by the PI. Instead, it will be performed by a different researcher (the co-author) who was not involved in the teaching process, using a dataset in which the group assignment is masked (coded as Group A vs. Group B).

To maintain this blinding and prevent the participants from distinguishing between the narrative formats (generic vs. adapted), the intervention relies on the physical and temporal separation of the clusters. Since Group A and Group B attend consecutive but distinct shifts, there is no simultaneous visual contact with the screens of the Control and Experimental groups. Furthermore, the clinical content and the structure of the Google Forms (Google LLC, Mountain View, CA, USA) remain visually identical for both groups; only the Wix interface ‘wrapping’ differs, and this is not visible to the other group due to the shift separation.

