The total cohort of 38 students will be divided into two consecutive practice shifts (Group A and Group B): one with 18 students and the other with 20. In the first session, software will be used to randomly assign which group will have the first shift. Students will remain in their assigned group for all four sessions to avoid cross-contamination. The program consists of four compulsory thematic modules:-Session 1: Prenatal care;-Session 2: Maternal-fetal assessment and well-being;-Session 3: Obstetric risk triage;-Session 4: Critical management in pregnancy.

Each day of the internship follows the same 120 min (2 h) time structure, which is visually summarized in Figure 2.

During the middle 60 min (intervention), the PI will monitor activity as the students interact with their devices. In the CG, all learners receive the same login URL and password, and the storytelling in Wix is standard. The mechanics are the same for everyone: progress bars are present, and points are awarded for correct answers. In the EG (PPDS-Adapted Gamification), at the beginning of each session, the PI provides differentiated codes (according to role) based on the learner’s profile to access five parallel narratives in Wix for the same clinical case. The clinical goal is the same for all participants, but the narrative “wrapping” and side mission change.

To ensure fidelity, the PI will be the only person with admin privileges in Wix and access to the Google Forms answers in real-time. Attendance will be monitored using signatures. The PI will resolve technical or clinical questions during the session, ensuring that the password lock in Wix does not impede the progress of learning.

Forms will be set up as “required steps” within the Wix narrative. In the case of the EG, the knowledge forms will be identical in content but esthetically matched to the identified player’s profile.

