## 4. Discussion

This protocol describes a pilot intervention designed to overcome the “one-size-fits-all” limitation in current simulation-based education. Although the literature supports the efficacy of gamification, there is a lack of reproducible methods to adapt these narratives to diverse student personalities on a large scale. The significance of this study lies in its use of Generative AI to make narrative personalization feasible and sustainable for standard nursing curricula, addressing the need for cost-effective implementation strategies. If successful, this protocol could serve as a blueprint for “Precision Education” [27] demonstrating how technology can drive the next era of personalized assessment [26]. In this model, training methodologies are tailored to the psychometric profile of the learner to maximize engagement and retention.

The necessity for such an adapted approach is underscored when comparing our proposed framework with the challenges highlighted in the recent literature. For instance, while studies [17] confirm that gamification generally enhances short-term motivation, they also warn of the ‘novelty effect’, where engagement drops if the digital environment fails to sustain a meaningful connection with the learner. Generic implementations often struggle with this, as a leaderboard that motivates a competitive student might actively demoralize a collaborative one. Furthermore, most contemporary research [20] still focuses on binary comparisons (gamification versus traditional lectures). By using generic gamification as the active control group, our protocol aims to move the conversation beyond mere technological implementation toward true precision education, isolating the specific pedagogical value of psychological profiling.

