**Figure 2 nursrep-16-00104-f002:**

Schematic diagram of the daily 120 min session workflow.

**Table 1 nursrep-16-00104-t001:** Comparison of gamification elements between control and experimental groups.

Element	Control Group (Generic)	Experimental Group (Adapted to Profile)
Clinical Difficulty	Invariant. Identical clinical cases and complexity.	Invariant. Identical clinical cases and complexity.
Narrative Tone	Neutral, academic, and linear.	Adapted, e.g., “Epic/Heroic” for Tryhard; “Humorous/Satirical” for Joker; “Emotional/Empathetic” for Socializer.
Visual Esthetics	Standard medical imagery (clean, white/blue).	Adapted, e.g., “High-fantasy/Dark” for Esthetic; “Leaderboards/Badges” prominence for Tryhard.
Feedback Style	Correct/incorrect + standard explanation.	Adapted, e.g., “Challenge failed, try again!” (Tryhard) vs. “Don’t worry, let’s learn together” (Coacher).
Side Missions	None.	Specific: Hidden “Easter eggs” (Joker), esthetic puzzles (Esthetic), or speed challenges (Tryhard).

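### The generic comparator does not isolate personalization: the experimental arm also receives side missions and themed content that no arm receives unmatched to profile

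*Protocol article*

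**What the plan says.** The Introduction presents the fit between game mechanics and player profile as the novel, testable contribution. It then says that "generic gamification was chosen as the active comparator to isolate and quantify the specific added value of the" 'personalization' variable. The Discussion says the active control moves the field forward by "isolating the specific pedagogical value of psychological profiling".

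Table 1 and section 2.7 describe the arms:

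- **Control arm.** Table 1 reads "Side Missions None". The narrative is "Neutral, academic, and linear", with standard medical imagery. Section 2.7 gives the mechanics as the same for everyone: "progress bars are present, and points are awarded for correct answers".
- **Experimental arm.** There are five parallel narratives per theme, with adapted tone, visuals and feedback. The side missions are hidden Easter eggs (Joker), "esthetic puzzles (Esthetic), or speed challenges (Tryhard").
- **Held constant.** Clinical case, difficulty, learning objectives and multiple-choice questions are the same in both arms.

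On the forms, section 2.5 says that the clinical content and the structure of the Google Forms "remain visually identical for both groups" and that only the Wix wrapping differs. Section 2.7 says of the experimental arm that "the knowledge forms will be identical in content but esthetically matched" to the player profile. Section 2.9 puts the knowledge tests on paper only and uses Google Forms only as digital locks.

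**The concern.** A comparator isolates a component when the arms differ in that component and in nothing else that could move the outcome. Here the experimental arm differs in being matched to profile and also in receiving game content that the control arm does not get in any form. If learning gain differs, the protocol's wording would credit profiling. Yet side missions or themed material given to everyone regardless of profile might have produced the same difference.

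This matters beyond the pilot. Section 2.4 says the estimated effect size will feed the power calculation for later multicenter trials, and section 5 says the data will help decide whether a precision-education approach merits larger trials. A package effect labelled as a personalization effect would carry that mislabelling into both decisions.

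**Working it through.** No arithmetic applies, since the protocol states no effect size, standard deviation or power. The check is an element-by-element comparison of the arms, followed by the question of what the primary contrast can identify.

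**Step 1. Compare the arms (Table 1 and section 2.7).**

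| Element | Control | Experimental | Nature of the difference |
|---|---|---|---|
| Clinical difficulty | Same | Same | None |
| Narrative tone | Neutral, one version | Themed by profile | Theming and matching together |
| Visuals | Standard | Themed by profile; leaderboards and badges more prominent for Tryhard, given as an example | Theming and matching together |
| Feedback | Correct/incorrect with standard explanation | Adapted; section 2.7 limits the change to tone | Tone and matching together |
| Side missions | None | Profile-specific | Added content and matching together |

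One element of five is invariant and four differ. Three of those four change the form of something both arms have. The fourth, side missions, is present in one arm and absent in the other.

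**Step 2. Write down what the contrast estimates.** Let E be the effect on learning gain of receiving the extra and themed game content whatever the student's profile. Let M be the further effect of matching that content to the profile. Let C be the difference between the two practice shifts themselves. Section 2.10 compares global learning gain between the two arms, so:

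expected difference (experimental − control) = E + M + C.

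The isolation claim requires this to equal M. The protocol acknowledges C in section 4.1. It does not acknowledge E.

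**Step 3. Look for any other contrast that would separate E from M.** Section 2.2 has two arms with one cluster each. By design every student in the experimental arm receives the code for their own profile, and every student in the control arm receives the plain version. No group has E without M. The profile analyses in section 2.10 are descriptive only and stay within this same structure, so they supply no matched-versus-unmatched comparison. M cannot be recovered.

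**Step 4. Consider the direction.** Both arms share the same 60-minute intervention block and the same clinical content. Side missions might raise engagement, or might take time from the clinical task. E could be positive or negative, so a null result is as ambiguous about matching as a positive one.

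**Step 5. Check whether the protocol covers it elsewhere.** Section 4.1 discusses sample size, the single cluster per arm, novelty, teacher bias, self-report and contamination. It does mention that control students may learn of the other arm's special missions, but only as a contamination and demotivation risk. The novelty paragraph attributes novelty to Wix, which both arms use. The bundling itself is not named.

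**Step 6. Check the forms.** If the knowledge forms in section 2.7 are the Google Forms, their profile-matched look conflicts with section 2.5, where only the Wix wrapping differs. If they are the knowledge tests, the statement conflicts with section 2.9, where the tests are on paper and separate from the platform. Either way the sections need reconciling.

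**The case against.** The strongest reply is that the formal aim and primary hypothesis in the Introduction already compare a profile-adapted intervention with a generic one, and that section 2.7 openly counts motivational mechanics as part of the adaptation. On that view the package is the treatment and the contrast is legitimate. This stands: neither the hypothesis nor the primary test needs to change. It does not rescue the two sentences that claim isolation.

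A second reply is that the protocol calls its inference exploratory and disclaims confirmatory evidence of superiority (sections 2.4, 2.10 and 4.1). That limits the harm, and a reader should not infer that the protocol would present a positive result as proof that profiling works. But those caveats concern sample size and one cluster per arm. A larger trial with many clusters and the same two arms would still estimate E + M.

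Several stronger readings are tempting and are not supported:

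- **The experimental arm loses the standard explanation.** Section 2.7 confines the feedback change to its tone, and the Table 1 entries are examples.
- **The whole experimental arm gains leaderboards and badges.** Table 1 mentions only their prominence, for Tryhard, as an example. Side-mission examples likewise cover three of the five profiles, so the amount of added content per profile is not fully specified.
- **All four differing elements are confounders.** Adapting tone, visuals and feedback is the personalization under study. Only side missions are unequivocally an addition.
- **The outcome instrument differs between arms.** Section 2.9 puts the tests on paper, and section 2.7 says the questions are identical. What is missing is one clear statement that the paper tests are the same in both arms.

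**Conclusion.** The point holds as a mismatch between claim and design. The trial can estimate, subject to the single-cluster limitation that it already admits, the effect of a profile-adapted package against a generic one. It cannot isolate the value of personalization or of psychological profiling, because side missions exist in one arm only and no students receive such content unmatched. The share of any difference due to matching is not identifiable, and the documents give no basis for a figure or a direction.

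The conclusion rests on Table 1's unambiguous entry for side missions and on the two-arm structure. It does not depend on the feedback or leaderboard entries. The disagreement about the forms is a smaller, separate inconsistency.

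**What to change.** 1. In the Introduction and the Discussion, replace the isolation claim with the effect of a profile-adapted gamification package versus a generic one, in line with the stated aim. Use the same description where results will be interpreted or used for planning: sections 2.4, 3 and 5.
2. Add a limitation to section 4.1: added game content and profile matching are bundled in the experimental arm, the contrast cannot separate them, and a larger trial of the same form would not do so either.
3. Optionally, give the control arm a generic side mission of equal length in each of the four sessions. This removes the one clearly additive element. It reduces the bundling without removing it, because themed narrative and visuals would still come together with matching.
4. Reconcile sections 2.5 and 2.7 on the appearance of the forms, and state in section 2.9 that the paper knowledge tests are identical in both arms.

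Items 1, 2 and 4 cost a few sentences. Item 3 costs the drafting of four generic side missions, and its downside is a smaller contrast between the arms. If a later trial wants to claim the value of matching itself, it needs participants who receive the adapted narratives without regard to their profile.

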## 2. Materials and Methods

### 2.1. Administrative Information

This manuscript represents Protocol Version 1.0, dated 16 January 2026. The primary sponsor for this study is the University of Atlántico Medio. The sponsor had no role in the design of this study and will not have any role during its execution, analysis, interpretation of the data, or decision to submit results. The protocol has been submitted for registration to ClinicalTrials.gov. The registration is currently pending validation.

### 2.2. Study Design

A cluster-randomized, prospective, comparative, and longitudinal pilot trial with two parallel groups is proposed. The study employs a 1:1 allocation ratio (one cluster per arm) and follows a superiority framework regarding the primary hypothesis. The CG will receive a generic gamified intervention, and the EG will receive an adapted gamified intervention. The study timeline spans four consecutive weeks. Participant flow, from enrollment to close-out, follows the schedule of assessment detailed in Figure 1.

The research questions and outcome measures were developed by the teaching faculty based on curricular requirements. Students were not involved in the design, recruitment, or conduct of this study. However, results will be disseminated to participants upon completion of the academic year.

### 2.3. Study Scope and Population

This single-center study will be carried out in an academic setting at the Faculty of Health Sciences of the University of the Atlántico Medio (Las Palmas de Gran Canaria, Spain) during the second semester of the 2025–2026 academic year. The target population will be second-year students of the bachelor’s degree in nursing enrolled in the course “Reproductive Health Nursing and Sex Education”.

The inclusion criteria are as follows: active enrollment, face-to-face attendance, and technological access. Students repeating the course, students with prior specialized training, and students with uncorrected sensory impairments will be excluded. The criteria for withdrawal once the study begins include incomplete data, abandonment of the session before the simulation is concluded, technological failure, or detected cross-contamination.

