### 2.10. Data Analysis

This publication constitutes the full trial protocol and detailed statistical analysis plan. No separate analysis plan document exists. Any future deviations from this plan will be reported and justified in the final results publication.

Data analysis will be carried out using the Jamovi 2.6.44 statistical package (The jamovi project, Sydney, Australia). Statistical significance level of *p* < 0.05 will be established; however, given the exploratory nature of these analyses, we will rely less strongly on *p*-values and give greater importance to effect sizes and 95% confidence intervals. In addition to statistical significance testing, the effect size and 95% confidence intervals will be reported for all primary outcomes. This approach prioritizes the estimation of the magnitude of the intervention effect, which is the primary statistical goal of this pilot study.

Before inferential analysis, the raw variables extracted from the forms 1F to 4F will be processed to generate the result metrics. The absolute LG will be calculated using the following formula: (PostTestScore) − (PreTestScore). To facilitate comparison, raw scores will be normalized to a standard grading scale of 0 to 10 points. This calculation will be applied consistently across all four sessions. To handle missing data, given the compulsory attendance requirement, a complete-case analysis approach will be utilized; participants with incomplete data for a session will be excluded from that specific analysis. Consequently, if a participant misses a session, their global LG metric will be calculated as the mean of their completed sessions only.

To handle the repeated measures design within the constraints of the pilot sample size, the primary analysis will not utilize complex mixed-model ANOVAs. Instead, the LG scores from the four sessions will be averaged to generate a global LG metric for each student. This summary measure is educationally meaningful as it reflects the overall assimilation of the obstetric module, mitigating the impact of performance fluctuations in any single session. This aggregation strategy aims to reduce intra-individual variance and provide a more robust estimator for the main group comparison. The normality of the dependent variables will be evaluated using the Shapiro–Wilk test. Given the estimated sample size, the use of non-parametric statistics is assumed to be a priority, unless the data demonstrates a normal distribution.

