Given the educational nature of the intervention, the risk of physical harm is negligible. However, specific protocols have been established to mitigate potential psychological, technical, and ethical risks. To ensure clinical and ethical safety, all narratives and clinical cases generated with the assistance of Generative Artificial Intelligence will be reviewed, corrected, and validated by the PI. This process guarantees that the content is free from gender bias, racial stereotypes, or erroneous clinical recommendations (hallucinations). To prevent potential offense or stigmatization arising from the PPDS profiles, students will be explicitly informed during the briefing that these categories are strictly playful archetypes for game mechanics and do not constitute a psychological or clinical diagnosis. In the event of persistent technical failures, the session will immediately revert to a traditional seminar format to prevent student anxiety or loss of learning time. The PI will maintain a “Field Diary” to record any spontaneous reports of student distress, technical incidents, or expressions of dissatisfaction. Any event requiring the interruption of a student’s participation will be reported to the Ethics Committee.

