As the researcher is also the teacher who evaluates the coursework, this could introduce unconscious bias (Pygmalion Effect) to favor the EG or generate in the students a desire to please the teacher by responding positively to the surveys. To address this situation, the knowledge-assessing questionnaires contain multiple-choice questions to facilitate automatic and objective correction and eliminate subjectivity on behalf of the evaluator. Anonymity will be guaranteed for the satisfaction surveys to encourage honesty.

As for the profile self-evaluation through the PPDS, the classification of the students depends on their sincerity when answering the test. It may be that a “Toxic” student does not recognize themselves as such and marks “Coacher” answers due to social desirability, thus being assigned a narrative that does not correspond accurately to their profile. This issue will be addressed by clearly explaining that there are no “good or bad” profiles, thus reducing social pressure.

Another limiting aspect is the risk of contamination between groups. As students are classmates from the same faculty, the CG students may learn about the existence of the EG’s “special missions” and feel demotivated (demoralizing effect) or try to obtain the EG passwords. To address this issue, Wix login passwords will be changed on a per-session and group basis, and explicit confidentiality will be required as part of the “game contract”. To actively monitor this risk without increasing survey fatigue, the Principal Investigator will utilize the pre-established “field diary” to record any spontaneous student disclosures or observable evidence of cross-contamination between the shifts. Any detected contamination will be reported as a feasibility metric and factored into the interpretation of the exploratory efficacy results. While this observational approach is suitable for a pilot, future definitive trials will benefit from incorporating a formal self-report question to empirically measure cross-contamination rates.

Finally, as a logistical limitation, and given the nature of the study, failures in the faculty’s Wi-Fi connection, Wix server crashes, or problems with students’ mobile devices could interrupt the intervention. An alternative plan will be available, with changes in the teaching schedule agreed upon with the students so that a new practical session may be scheduled.

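### Section 2.3 withdraws students with incomplete data whom Section 2.10 keeps in the primary endpoint, so the primary analysis set is not fixed

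*Protocol article*

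**What the plan says.** All references are to the Protocol article.

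- **Section 2.3 (Study Scope and Population):** the "criteria for withdrawal once the study begins include incomplete data, abandonment of the session before the simulation is concluded, technological failure". The list ends with "technological failure, or detected cross-contamination".
- **Section 2.10 (Data Analysis):** under a stated complete-case approach, "participants with incomplete data for a session will be excluded from that specific analysis", and "if a participant misses a session, their global LG metric will be calculated as the mean of their completed sessions only". The same section says that the article is the full analysis plan and that there is no separate one.
- **Section 4.1 (Limitations), on contamination:** "Any detected contamination will be reported as a feasibility metric and factored into the interpretation of the exploratory efficacy results".
- **Section 2.11 (Data Protection and Trial Management), on technical failure:** "In the event of persistent technical failures, the session will immediately revert to a traditional seminar format".
- **Section 4.1, on technical failure:** the teaching schedule may be changed "so that a new practical session may be scheduled".

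The primary endpoint is the average of four session LGs on a 0 to 10 scale, one for each of four different topics (Sections 2.7, 2.8 and 2.10). Retention and technical failure rates are formal feasibility outcomes (Section 2.8).

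**The concern.** A student who lacks one post-test is withdrawn under Section 2.3 and analysed on three sessions under Section 2.10. Because all students attend the sessions as ordinary coursework and only consented data are processed (Section 2.6), withdrawal from the study can hardly mean anything other than loss of that student's data. The two rules therefore define two different primary analysis sets. With no other plan to settle the matter, the choice would fall to whoever prepares the data set, possibly after results are visible.

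Three things are at stake. The first is the effect size and variance estimate, which Sections 2.4 and 2.10 give as the purpose of the pilot. The second is the retention rate, which changes with the definition of withdrawal. The third is the fairness of the arm contrast: every listed criterion arises after allocation. Contamination is described in Section 4.1 as control group (CG) students learning of, or trying to reach, experimental group (EG) content. It is recorded in a field diary by the PI, who is unblinded during the sessions (Section 2.5). Exclusions on that basis could fall unequally on the arms.

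A smaller point concerns the endpoint itself. If sessions differ in expected gain, a mean over three sessions does not measure quite the same thing as a mean over four.

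**Working it through.** **The plan's own figure.** The sample size is a convenience sample of 38 with no power calculation (Section 2.4), so there is none to reproduce. The shift sizes agree with it: 18 + 20 = 38.

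**Step 1. The rules side by side.**

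| Event | Section 2.3 | Elsewhere | Status |
|---|---|---|---|
| Incomplete data | Withdrawn | 2.10: kept, mean of remaining sessions | Direct contradiction |
| Detected contamination | Withdrawn | 4.1: reported and weighed in interpretation | Analysis status not stated |
| Technical failure | Withdrawn | 2.11: seminar; 4.1: possible new session | Session managed; status of the data not stated |

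The complete-case label does not fit global LG either. A complete-case analysis of a four-session mean would use only students with all four sessions, whereas the rule in Section 2.10 is an available-session mean.

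**Step 2. Size of the analysis set under each rule.** The documents give no loss rate. Let m be an assumed probability of losing a session, independent across sessions, and read incomplete data in Section 2.3 as any one incomplete session.

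- Section 2.3: expected n = 38(1 − m)^4
- Section 2.10: expected n = 38(1 − m^4), since one completed session is enough

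| Assumed m | Section 2.3 | Section 2.10 |
|---|---|---|
| 2% | 35.0 | 38.0 |
| 5% | 31.0 | 38.0 |
| 10% | 24.9 | 38.0 |
| 15% | 19.8 | 37.98 |

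**Step 3. Shift in global LG when one session is lost.** Let M be the mean gain of the other three sessions and M − D that of the lost one. The four-session mean is (3M + M − D)/4 = M − D/4, and the available-session mean is M. The shift is D/4. No session gains are given, so D is an assumption:

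- D = 0: shift 0
- gains 4, 3, 3, 2 with the last session lost: D = 10/3 − 2 = 1.33, shift 0.33
- D = 2: shift 0.50

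**Step 4. Effect on the arm contrast.** This was simulated with the two-sided Mann–Whitney test, 18 versus 20 students, no treatment effect, 4,000 runs, and an assumed SD of 1 point both between and within students. Assumed gains were 4, 3, 3, 2, with the last session lost in the EG only.

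| EG students losing the session | Shift in contrast | Rejection rate (nominal 5%) |
|---|---|---|
| 0 of 20 | 0.02 (simulation noise) | 4.9% |
| 4 of 20 | 0.07 | 5.2% |
| 10 of 20 | 0.17 | 7.6% |
| 20 of 20 | 0.34 | 13.6% |

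With equal gains in all sessions, the rejection rate stays between 4.4% and 5.2% in every case. Scattered losses are harmless; only a loss concentrated in one arm matters.

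**Step 5. Would centring each session on its pooled mean repair this?** Suppose the true effect is δ in every session, and the EG (n = 20) lacks one session entirely. In the three shared sessions the centred means are 18δ/38 (EG) and −20δ/38 (CG). In the fourth session the pooled mean is the CG mean, so the CG contributes 0. The contrast is 18δ/38 + (3/4)(20δ/38) = 33δ/38 = 0.868δ, an attenuation of 13.2%. If the arm that lacks the session has 18 students, it is 20δ/38 + (3/4)(18δ/38) = 33.5δ/38 = 0.882δ, or 11.8%. Centring therefore costs about 12 to 13% of a true effect in just the case where an adjustment is needed.

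**The case against.** The strongest reply is that most of this is loose wording in a pilot. Sections 2.4, 2.10 and 4.1 call the efficacy comparison exploratory. Section 4.1 concedes that one cluster per arm confounds the effect with cluster differences, which no missing-data rule can cure. Sections 2.8 and 2.9 already record retention, technical failure, contamination and the reasons for missing sessions. This stands, and it lowers the severity. It does not remove the conflict on incomplete data, which bears on the estimates the pilot exists to produce.

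A reader might also infer more than the documents support:

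- **That one platform outage deletes a session for a whole arm.** Section 2.9 puts the knowledge tests on paper so that data collection does not depend on the platform, and a seminar or a new session can still yield scores. The whole-arm row in the simulation is an outer bound, not an expected result.
- **That Section 4.1 keeps contaminated students.** It does not say so. Reporting contamination is compatible with withdrawing them, so this is a gap and not a second contradiction.
- **That technical failure has three rival analysis rules.** Sections 2.11 and 4.1 manage the session, and a seminar now with a new session later can coexist. What is missing is whether the data count.
- **That technical failure depends on arm.** Both arms use Wix and the same form-based locks, and the failures named in Section 4.1 are common to both. Only contamination is described asymmetrically.
- **That session gains do differ.** Different topics make this possible, not established.

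**Conclusion.** The concern holds in a limited form. Sections 2.3 and 2.10 contradict each other on incomplete data. For contamination and technical failure, the withdrawal criterion in Section 2.3 is not tied to any analysis rule elsewhere. As written, the primary analysis set cannot be determined: about 31 versus 38 students at an assumed 5% independent loss per session, and about 25 versus 38 at 10%. Withdrawal for contamination, a post-allocation event recorded by an unblinded teacher, can bias the contrast; the documents do not allow the size of that bias to be calculated.

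The available-session mean is a secondary issue. Its shift runs from 0 with equal gains to 0.5 points per affected student at an assumed D of 2, and it is negligible for scattered losses. The severity is should-fix rather than must-fix, because the comparison is declared exploratory.

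**What to change.** 1. Reconcile Sections 2.3, 2.10, 2.11 and 4.1 so that each listed event has one stated consequence for the data, including whether a seminar or rescheduled session counts as completed.
2. Define the primary analysis set as every consenting student with at least one paired pre- and post-test score, in the allocated arm. Count incomplete data, early departure, technical failure and contamination as feasibility outcomes, and show results without the affected students only as a sensitivity analysis.
3. Drop the complete-case label for global LG and call it an available-session mean.
4. If any sessions are missing, add a sensitivity analysis that accounts for session: LG on arm and session with a student random intercept. This assumes the same arm effect in each session. It is preferable to pooled-mean centring because of the attenuation shown above. The simple summary measure chosen in Section 2.10 remains the primary analysis.

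The cost is a few sentences of protocol text and one extra analysis. No further data collection is needed.
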